**3.3 Exclusion criteria**

The exclusion criteria will:

1. Patients who are pregnant or breast feeding
2. Patients who are not undergoing contraceptive treatments
3. Patients who have taken antibiotics and/or probiotics within the previous 3 months
4. Patients who have had a positive glucose breath test in the past
5. Patients with an organic colonic or anorectal disease (cancer, ischemia, infection, etc.)
6. Patients with an autonomic diabetic neuropathy, dysthyroidism, coeliac disease, or connective tissue disease
7. Patients who have undergone intestinal surgery (except cholecystectomy or appendectomy)
8. Patients with a psychiatric disorder
9. Patients who have participated in another medicinal product study during the 30 days preceding the inclusion visit
10. Patients who are allergic to metronidazole
11. Patients who do not speak or read French
12. Patients who are no longer autonomous

Patients who are taking a treatment (laxative, anti-diarrheic treatment, morphine, antidepressant, etc.) that may interfere with their gastro-intestinal motility or sensitivity will be asked to continue their treatment during the study. In the event of a significant change during the study, the patient will be excluded.

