8.8 Confidentiality

8.9 Archiving

**9. PUBLICATIONS**

**10. BIBLIOGRAPHY**

**1. STATE OF SCIENTIFIC KNOWLEDGE**

Anal incontinence is a public health problem because of its prevalence (Denis, 1992). Anal incontinence includes the accidental passing of solid or liquid stools via the rectum (fecal incontinence) and the involuntary leakage of gas (flatus incontinence). Flatus incontinence is the most common type of anal incontinence, with a prevalence estimated at approximately 33% in the general adult population (Damon, 2006). Although flatus incontinence appears to have less impact upon quality of life than fecal incontinence (Boreham, 2005), it is an embarrassing and socially restricting problem (Steinberg, 2009; Meyer, 2015). The management of flatus incontinence is challenging. Conservative medical (biofeedback) and surgical (sacral nerve stimulation, artificial bowel sphincter) strategies used to treat fecal incontinence are often disappointing in terms of reducing gas leakages (Michot, 2003; Leroi, 2009). Medications such as simethicone/activated charcoal are used to relieve gaseous symptoms, but the few studies on their efficacy have reported contradictory results (White, 1991; Friis, 1991).

Flatus incontinence is associated with anal sphincter weakness and can be exacerbated by excessive rectal gas production (Di Stefano, 2000), which can be caused by small intestinal bacterial overgrowth (SIBO). SIBO is defined as a bacterial population in the small intestine exceeding 10^5^–10^6^ organisms/mL (Simren, 2006). Symptoms of SIBO include diarrhea, weight loss, anemia, and intestinal malabsorption. Gastrointestinal tract surgeries that create blind loops (jejuno-ileal bypass, end-to-side enteroenteric anastomosis) as well as small bowel motility disorders (sclerodermia, intestinal pseudo-obstruction) predispose to bacterial stasis and overgrowth. SIBO has also been observed in patients with irritable bowel syndrome or dyspepsia (Pimentel, 2000; Pimentel, 2003). SIBO is generally diagnosed using glucose hydrogen (H_2_) and methane (CH_4_) breath tests.

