**2. AIMS OF THE STUDY**

The aims of the study are to compare the efficacies of a conventional therapy and of an antibiotic therapy for treating SIBO diagnosed by the glucose breath test and to determine whether the antibiotic treatment improves flatus incontinence.

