**3.4 Patient selection**

All patients who consult for flatus incontinence or for predominant flatus incontinence in the case of associated fecal incontinence (i.e., occasional fecal incontinence episodes with fewer than one episode per month) will be asked if they are interested in participating in the study.

Each patient will complete a self-assessment questionnaire about their continence disorder and their digestive symptoms, including the Rome 3 criteria. Each patient will also undergo a medical examination during which a questionnaire about their medical and surgical histories, current treatments, including contraceptive treatments, will be completed. A clinical examination will also be performed. Patients with anal incontinence will not undergo a comprehensive continence assessment (anorectal manometry, endoanal ultrasound, electrophysiologic tests) because flatus incontinence is often refractory to treatments that are usually indicated for fecal incontinence and because such an assessment will not be helpful in choosing the most appropriate treatment.

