**3.6 Study design and randomization**

All patients referred for flatus incontinence will undergo a glucose breath test. In the event of a positive glucose breath test, the patients will be asked to complete a 3-day bowel diary prior to randomization.

The patients will receive:

- Metronidazole (Flagyl^®^ per os, 500 mg, 3 per day for 10 days), or
- Carbosylane^®^ (45 mg of simethicone and 140 mg of activated charcoal per capsule, 3 capsules per day for 10 days.

The choice of antibiotic was empirical because of the small number of studies investigating the efficacy of antibiotics for treating SIBO and the lack of consensus. Large spectrum antibiotics appear to be the most appropriate antibiotics since they are effective against both aerobic and anaerobic bacteria. Rifaximin appears to be more effective than tetracycline and is not absorbed after oral ingestion, limiting the secondary effects. Unfortunately, rifaximin is not commercially available in France. One controlled study has shown that metronidazole is more effective than rifaximin in reducing the symptoms of SIBO and returning glucose breath test results to normal values [Di Stefano, 2005]. Another controlled study, which compared norfloxacin, clavulanic acid-amoxicillin, a probiotic, and a placebo [Attar, 1999] showed that norfloxacin and clavulanic acid are more effective for treating diarrhea in patients with SIBO than other treatments. Norfloxacin and metronidazole are the most frequently used antibiotics in France for treating SIBO. The minor and moderate secondary effects of norfloxacin and metronidazole are comparable in frequency. However, norfloxacin causes more frequent serious secondary effects than metronidazole, which is why we opted for metronidazole.

A symptomatic evaluation and a glucose breath test (for patients in the group receiving metronidazole) will be performed after the 10-day treatment.

Patients treated with Carbosylane^®^ may be given a course of antibiotics at the end of the study in the event they have persistent digestive symptoms. The results of this antibiotic treatment will not be taken into consideration for the purposes of the study.

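### Section 3.3 restricts earlier antibiotics and probiotics but not simethicone/charcoal, the comparator itself, so a baseline diary can already contain the comparator's effect; the likely direction favours metronidazole, by an unknown amount.

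*Protocol*

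**What the plan says.** - **Entry restriction on earlier treatment.** Section 3.3, item 3 excludes "Patients who have taken antibiotics and/or probiotics within the previous 3 months". None of the 12 exclusion criteria names simethicone or activated charcoal, and no washout or run-in for them appears elsewhere in the protocol.
- **Comparator.** Section 3.6 defines Carbosylane as "45 mg of simethicone and 140 mg of activated charcoal per capsule", given for 10 days. The aim in section 2 is to "compare the efficacies of a conventional therapy and of an antibiotic therapy".
- **Existing use.** Section 1 states: "Medications such as simethicone/activated charcoal are used to relieve gaseous symptoms". It adds that "the few studies on their efficacy have reported contradictory results".
- **Concomitant treatment.** The closing paragraph of section 3.3 says that patients on treatments that may affect gut motility or sensitivity "will be asked to continue their treatment during the study". Its list of examples is open-ended and does not name simethicone or charcoal. A significant change during the study leads to exclusion.
- **Recording.** Section 3.4 says that "a questionnaire about their medical and surgical histories, current treatments, including contraceptive treatments, will be completed".
- **Baseline and outcome.** After a positive breath test, "the patients will be asked to complete a 3-day bowel diary prior to randomization" (section 3.6). The primary outcome is the percentage decrease in mean daily gas leakages from that diary to the one at the end of treatment. A reduction of more than 50% counts as a response.

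**The concern.** The protocol calls the comparator class conventional therapy, says it is already used for gas symptoms, and enrols patients referred for flatus incontinence. Current users are therefore foreseeable, and a site that follows the rules as written would admit them.

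For such a patient the baseline diary measures the leakage rate with the comparator already acting. Allocation to Carbosylane then offers roughly what the patient already takes, so little further decrease can appear. A user allocated to metronidazole can still show that drug's effect, and nothing stops that patient from taking the comparator product as well.

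Randomisation does not remove this. Equal numbers of users in the two arms still leave one arm with less effect to show. Eligibility and the handling of concomitant products are fixed in the protocol, and no later analysis can recover an untreated baseline. At stake is whether a between-arm difference reflects the antibiotic or earlier exposure to the control product.

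**Working it through.** The protocol states no figure that could be reproduced here. Section 4.1 calls the 20 per arm arbitrary and gives no effect size. The check is therefore on direction and on what drives the size.

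**Inputs, all assumed.** *m* and *c* are the true proportional reductions with metronidazole and with simethicone/charcoal, and effects multiply. *u* is the share of current users at entry, equal in both arms. An untreated rate of 1 is taken as reference, so a user's baseline is 1 − *c*.

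**With no users (*u* = 0).** The expected difference in percentage decrease is *m* − *c*.

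**Case A: users continue their own product, and the study capsules add nothing to it.**
- Metronidazole arm: every patient shows *m*, because a user goes from (1 − *c*) to (1 − *c*)(1 − *m*).
- Carbosylane arm: non-users show *c* and users show 0, so the mean is (1 − *u*)*c*.
- Difference: *m* − (1 − *u*)*c*. The shift is *u* × *c* towards metronidazole.

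**Case B: users stop their own product at randomisation.**
- Metronidazole arm: a user goes from (1 − *c*) to (1 − *m*), a decrease of (*m* − *c*)/(1 − *c*).
- Carbosylane arm: a user goes from (1 − *c*) to (1 − *c*), a decrease of 0.
- Difference: (1 − *u*)(*m* − *c*) + *u*(*m* − *c*)/(1 − *c*) = (*m* − *c*)[1 + *u* × *c*/(1 − *c*)].

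**Results, difference in percentage points (metronidazole minus Carbosylane):**

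| *m*, *c* | True | Case | *u* = 10% | 20% | 30% | 50% |
|---|---|---|---|---|---|---|
| 30%, 30% | 0 | A | 3 | 6 | 9 | 15 |
| 30%, 30% | 0 | B | 0 | 0 | 0 | 0 |
| 40%, 20% | 20 | A | 22 | 24 | 26 | 30 |
| 40%, 20% | 20 | B | 20.5 | 21.0 | 21.5 | 22.5 |
| 20%, 30% | −10 | A | −7 | −4 | −1 | 5 |
| 20%, 30% | −10 | B | −10.4 | −10.9 | −11.3 | −12.1 |

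**Three limits follow.**
- With *c* = 0, both formulas return *m*, so there is no shift through the baseline.
- If the study capsules give a user a further decrease *k*, the case A shift becomes *u*(*c* − *k*). For example, *u* = 25% and *c* = 30% give 7.5 points with *k* = 0 and 0.25 × (30 − 10) = 5 points with *k* = 10%.
- In case B the shift only enlarges whatever true difference exists. It therefore favours the comparator slightly if the comparator is the better drug (last row).

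On the absolute change, which section 4.3 also compares, case B has no shift: a user contributes (1 − *c*) − (1 − *m*) = *m* − *c* on metronidazole and 0 on Carbosylane, a difference of *m* − *c* as in non-users.

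**The case against.** A reader might infer that the comparison, as designed, does tilt towards metronidazole. The documents do not support that as a fact.

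- The clear tilt needs users to continue their own product and the study capsules to add nothing. The protocol gives no information on earlier doses or dose-response.
- If users stop at randomisation, the shift is zero for equal effects and small otherwise.
- The comparator may do nothing. Section 1 itself calls the evidence contradictory.
- Section 1 speaks of gas symptoms in general and gives no usage rate among patients referred for flatus incontinence.

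A reader might also infer that patients enter after the product has failed them and are selected non-responders to the control arm. That is plausible, but nothing in the protocol shows how many such patients there are. Nor can one say that item 3 exists only to protect the antibiotic comparison, since it may equally protect the breath-test diagnosis.

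It can also be said that this is a pilot of arbitrary size in a referral population, where admitting earlier users is a defensible pragmatic choice, and that section 3.4 already records current treatments.

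These points limit certainty and size; they do not close the gap. Recording a treatment does not restrict it, and a recorded user still enters. The concomitant-treatment paragraph does not settle the matter either. If simethicone/charcoal falls within its open list, users continue (case A) and stopping could count as a change that leads to exclusion. If it does not, the protocol is silent and the two centres may act differently.

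**Conclusion.** The gap is real. The comparator product is unrestricted before and during the baseline diary and outside the allocated treatment, while the primary outcome is a percentage decrease from that diary. The likely direction favours metronidazole, because the main route (case A) reduces what the Carbosylane arm can show and leaves metronidazole's effect in place.

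The size is unknown. Under case A it is *u* × *c*, that is 3 to 15 points for 10% to 50% users at an assumed 30% comparator effect. Under case B it is nil at equal effects and at most 2.5 points in the settings tabulated. It is nil through the baseline if the comparator is inert. With 20 per arm, five users would already be 5/20 = 25% of an arm. The point supports a protocol change that costs little. It does not support a claim that a difference favouring metronidazole would be spurious.

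**What to change.** 1. Add to section 3.3, beside item 3, an eligibility criterion covering current or recent use of simethicone/activated charcoal before the baseline diary. The interval is for the sponsor to set.
2. State that non-study use of the comparator product is not part of either arm from the baseline diary to the end-of-treatment diary.
3. Reconcile this with the closing paragraph of section 3.3, so that it is clear whether these products fall under the request to continue and the exclusion for significant change.
4. Use the current-treatment data already collected under section 3.4 to identify users. No new form is needed for that.

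I would not rely on an added analysis in patients who never used the product. With about 20 per arm to start from, it would say little, and it is no substitute for an eligibility rule.

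The cost is a short protocol amendment and, among current users, a short delay before the baseline diary or a few exclusions.

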**3.4 Patient selection**

All patients who consult for flatus incontinence or for predominant flatus incontinence in the case of associated fecal incontinence (i.e., occasional fecal incontinence episodes with fewer than one episode per month) will be asked if they are interested in participating in the study.

Each patient will complete a self-assessment questionnaire about their continence disorder and their digestive symptoms, including the Rome 3 criteria. Each patient will also undergo a medical examination during which a questionnaire about their medical and surgical histories, current treatments, including contraceptive treatments, will be completed. A clinical examination will also be performed. Patients with anal incontinence will not undergo a comprehensive continence assessment (anorectal manometry, endoanal ultrasound, electrophysiologic tests) because flatus incontinence is often refractory to treatments that are usually indicated for fecal incontinence and because such an assessment will not be helpful in choosing the most appropriate treatment.

**3.5 Breath testing**

Several methods have been used to diagnose SIBO [Romagnuolo, 2002]. We chose the glucose breath test because (1) it provides excellent inter-observer reproducibility (100%), which is not the case, for example, for the lactulose breath test, (2) 100% of a 75 g dose of glucose is completely absorbed in the duodenum and, as such, there is no risk of a positive glucose breath test due to the arrival of glucose in the colon and the transit time in the small intestine does not have to be taken into consideration, and (3) it has the sensitivity and specificity required to diagnose SIBO [Fine, 1999].

The glucose breath test will be performed using a previously published method [Johlin, 2004]. Patients will be asked to avoid ingesting unfermentable carbohydrates (e.g., whole grain breads, pasta) in order to reduce the production of H_2_ during the two days preceding the test. Patients will be asked to fast overnight. Good oral hygiene will be recommended the day before and the morning of the test. Smokers will be asked to avoid smoking for 1–2 h prior to the test. Patients will be asked to avoid exercise for 2 h prior to the test. Patients will be asked to rinse their mouths with a antiseptic chlorhexidine solution prior to the test to eradicate oral bacterial flora. Patients will be asked to ingest 75 g of glucose dissolved in 250 mL of water. Breath samples will be collected at baseline and at 15-min intervals for 2 h in a bag (QuinTron Instrument Company, Inc.). Hydrogen and methane levels in the alveolar gas will be analyzed by chromatography (QuinTron Micro Analyzer, QuinTron Instrument Company, Inc.). Patients will be asked to complete a questionnaire listing their symptoms following the ingestion of the glucose.

The glucose breath test will be considered positive for SIBO if at least one of the following criteria are met: (i) ≥10 ppm increase above H_2_ and/or CH_4_ baseline values for at least two consecutive measurements; (ii) ≥10 ppm increase between minimum and maximum H_2_ and/or CH_4_ values over the 2-h breath collection period; and (iii) 20 ppm of H_2_ and/or CH_4_ at baseline if the patient followed the preparation guidelines [Romagnuolo, 2002].

**3.6 Study design and randomization**

All patients referred for flatus incontinence will undergo a glucose breath test. In the event of a positive glucose breath test, the patients will be asked to complete a 3-day bowel diary prior to randomization.

The patients will receive:

- Metronidazole (Flagyl^®^ per os, 500 mg, 3 per day for 10 days), or
- Carbosylane^®^ (45 mg of simethicone and 140 mg of activated charcoal per capsule, 3 capsules per day for 10 days.

The choice of antibiotic was empirical because of the small number of studies investigating the efficacy of antibiotics for treating SIBO and the lack of consensus. Large spectrum antibiotics appear to be the most appropriate antibiotics since they are effective against both aerobic and anaerobic bacteria. Rifaximin appears to be more effective than tetracycline and is not absorbed after oral ingestion, limiting the secondary effects. Unfortunately, rifaximin is not commercially available in France. One controlled study has shown that metronidazole is more effective than rifaximin in reducing the symptoms of SIBO and returning glucose breath test results to normal values [Di Stefano, 2005]. Another controlled study, which compared norfloxacin, clavulanic acid-amoxicillin, a probiotic, and a placebo [Attar, 1999] showed that norfloxacin and clavulanic acid are more effective for treating diarrhea in patients with SIBO than other treatments. Norfloxacin and metronidazole are the most frequently used antibiotics in France for treating SIBO. The minor and moderate secondary effects of norfloxacin and metronidazole are comparable in frequency. However, norfloxacin causes more frequent serious secondary effects than metronidazole, which is why we opted for metronidazole.

A symptomatic evaluation and a glucose breath test (for patients in the group receiving metronidazole) will be performed after the 10-day treatment.

Patients treated with Carbosylane^®^ may be given a course of antibiotics at the end of the study in the event they have persistent digestive symptoms. The results of this antibiotic treatment will not be taken into consideration for the purposes of the study.

If a patient displays secondary effects or develops an allergy to metronidazole or Carbosylane^®^, he/she will be excluded from the study and will be replaced by another patient. Given the number of patients that will potentially be excluded from the study following their inclusion, we plan on recruiting 50 patients in order to maintain a 20-patient cohort for each experimental arm (Carbosylane^®^ and metronidazole).

The main primary outcome will be the percentage decrease in the mean daily number of gas leakages reported in the 3-day diaries that will be completed before (baseline) and at the end of the 10-day treatment period and before the regimen performed prior to the glucose breath test. A positive clinical response will be defined as a greater than 50% reduction in the mean daily number of gas leakages.

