**4. DATA ANALYSIS AND STATISTICS**

**4.1 Number of patients**

Due to the lack of a preliminary study on the efficacy of treatments for flatus incontinence, we were unable to determine a sample size and decided to arbitrarily enroll 20 patients in each group for the pilot study.

To maintain 20 patients in each experimental arm (i.e., 20 patients treated with Carbosylane^®^ and 20 with metronidazole), we plan to recruit 25 patients for each experimental arm to compensate for non-compliant patients and patients who develop allergies or intolerance to treatment, or who are lost at follow-up. The frequency of positive glucose breath tests in patients with flatus incontinence is difficult to estimate because this has never been investigated. However, we presume that one out of three patients will have a positive glucose breath test.

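### Randomised patients with side effects or allergy are excluded and replaced, so the comparison of metronidazole with Carbosylane is open to selection bias

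*Protocol*

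**What the plan says.** Three places in the protocol bear on who remains in the comparison.

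- **Section 3.6** states a rule for both arms: "If a patient displays secondary effects or develops an allergy to metronidazole or Carbosylane", then "he/she will be excluded from the study and will be replaced by another patient". It gives no severity threshold. The same paragraph continues: "we plan on recruiting 50 patients in order to maintain a 20-patient cohort for each experimental arm".
- **Section 3.3**, on treatments that may affect gastro-intestinal motility or sensitivity, states: "In the event of a significant change during the study, the patient will be excluded". It does not mention replacement.
- **Section 4.1** calls the 20 per group arbitrary and raises recruitment to 25 per arm "to compensate for non-compliant patients and patients who develop allergies or intolerance to treatment, or who are lost at follow-up". This implies that non-compliant patients are removed, but does not say so.

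Under section 3.6 the baseline diary is completed before randomisation, and the primary outcome needs a second diary at the end of the 10-day treatment. Section 4.3 compares the two groups without naming an analysis set. Nothing in the protocol keeps an excluded patient in follow-up or in the comparison.

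**The concern.** Side effects and allergy can occur only after the patient has been allocated and has taken the product. Non-compliance and a change of co-medication during the study also come after allocation, and either may be a reaction to the allocated drug. If such patients are taken out and others put in their place, the groups compared are those who tolerated metronidazole and those who tolerated Carbosylane. Randomisation does not make those two groups comparable.

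The removal rule also overlaps with the endpoints. Section 7.5 puts digestive disorders first among the possible effects of metronidazole. Section 3.1 lists abdominal pain, borborygmi, urgency and bowel-movement frequency as secondary endpoints. A patient whose digestive symptoms worsen on the drug can meet the exclusion rule and so drop out of the endpoint that would have recorded the worsening.

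This is more than a choice of analysis set that could be left to an analysis plan. A patient excluded during a 10-day treatment has no assured final diary, and an analysis plan cannot recover a diary that was never collected.

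**Working it through.** **1. The plan's own figure.** Section 4.1 gives 20 to be kept and 25 recruited per arm; section 3.6 gives 50 in total.

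- Allowance: 1 - 20/25 = 1 - 40/50 = 20%, that is 5 per arm and 10 in total.
- Check: 20/(1 - 0.20) = 25 per arm. The figure reproduces.

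The allowance covers non-compliance, allergy or intolerance, and loss to follow-up together. It is not split by reason or by arm.

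**2. What a result in the retained patients leaves open.** Suppose 8 of 20 retained patients in an arm respond (40%), and 5 of the 25 randomised were removed. The rate among all randomised lies between 8/25 = 32% (none of the 5 respond) and 13/25 = 52% (all 5 respond).

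**3. Spurious difference between arms.** Let p be the response rate in all randomised, set equal in both arms so that there is no true difference. Let q be the response rate among those removed, taken as the same in both arms. Let dM and dC be the shares removed on metronidazole and Carbosylane.

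- Rate among retained patients in an arm: (p - d x q)/(1 - d)
- Difference between arms: (p - q) x [dM/(1 - dM) - dC/(1 - dC)]

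The protocol gives none of these inputs, so all values below are assumptions.

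| dM | dC | Bracket | p = 30%, q = 10% | p = 50%, q = 10% |
|---|---|---|---|---|
| 20% | 10% | 0.250 - 0.111 = 0.139 | 0.20 x 0.139 = 2.8 points | 0.40 x 0.139 = 5.6 points |
| 30% | 5% | 0.429 - 0.053 = 0.376 | 0.20 x 0.376 = 7.5 points | 0.40 x 0.376 = 15.0 points |

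Over removal of 20-30% on metronidazole and 5-10% on Carbosylane, the range is about 3 to 15 points.

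**4. When it vanishes or shrinks.** If dM = dC, the bracket is 0. If q = p, the first factor is 0. With low removal, say 10% against 5%, the bracket is 0.111 - 0.053 = 0.058 and the difference is 1.2 points (p = 30%) to 2.3 points (p = 50%).

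**5. Effect on a test.** Take p = 50%, removal of 30% against 10% (20% on average, matching the allowance), and no responders among those removed. The retained rates are 0.5/0.7 = 71.4% and 0.5/0.9 = 55.6%, a gap of 15.9 points with no true effect. By exact enumeration at 20 per arm, a two-sided 5% pooled z-test rejects about 18% of the time, against about 4% when both retained rates are 50%.

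**The case against.** The strongest objection is that bias has not been shown. It needs unequal removal and different outcomes in those removed. Section 7.5 gives no frequencies, its silence on Carbosylane is not evidence that Carbosylane has no side effects, and section 8.1 describes metronidazole adverse events as relatively rare. This stands: the documents establish that the comparison is open to bias, not that it is biased or that metronidazole is favoured. But the sponsor did reserve one patient in five for such losses.

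A reader might infer several stronger points that the documents do not support:

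- **That all four kinds of patient are removed and replaced.** Replacement is stated only for side effects and allergy.
- **That 20% will leave for treatment-related reasons.** The 20% is a reserve and includes loss to follow-up.
- **That replacement comes on top of the 50.** Section 3.6 moves straight from replacement to the figure of 50, so the natural reading is that the 50 is the pool from which replacements come.
- **That tolerability can no longer be assessed.** Section 4.2 records secondary effects in the diaries and section 7.4 requires every adverse event to be recorded and registered. Nothing limits this to the retained patients. It protects safety reporting, but not the efficacy comparison.

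The illustration uses the responder rate, whereas section 3.6 makes the percentage decrease primary. That is a fair limit on the figures. The mechanism carries over, because the mean among retained patients has the same algebraic form.

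Finally, this is a pilot with an arbitrary sample size. Yet section 2 aims to compare efficacies and section 4.3 compares the groups, and a pilot particularly needs sound estimates of dropout and effect.

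**Conclusion.** The point holds in a limited form. The protocol fixes exclusion and replacement of randomised patients on grounds that arise after treatment starts, adds exclusion for a change of co-medication, and sizes recruitment to absorb losses. Up to 5 of 25 per arm may be lost from the comparison for reasons that include treatment effects, and no text retains them.

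The distortion in the responder rate can be zero. It is about 3 to 15 points under the assumed 20-30% against 5-10% removal, 10% response among those removed and 30-50% response overall. It would be smaller if removal is rare, and could run in either direction if removal or outcomes differ from these assumptions. The rule should be changed before recruitment, because final diaries not collected cannot be supplied later.

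**What to change.** Remove "he/she will be excluded from the study and will be replaced by another patient" from section 3.6, and the matching exclusion in section 3.3, as rules for follow-up and analysis. In their place:

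- Randomise the planned 50 with no replacement.
- Ask patients who stop study drug or change co-medication to complete the end-of-treatment diary.
- Make the primary comparison all randomised patients in their allocated arm. State in advance how a final diary that is still missing enters the percentage decrease.
- Add a sensitivity analysis of the greater-than-50% response in which patients without a final diary count as non-responders.
- Keep the tolerant, compliant set as a secondary per-protocol analysis.

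Whether to stop treatment remains a clinical decision; only follow-up and analysis change.

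The cost is protocol wording and a few extra diaries. No patients are added to the 50 already planned. The estimated effect may be slightly smaller than in the tolerant set.
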